#### Interventionists and training

Three Master’s level health professionals with prior training and experience using MI are trained to deliver all 3 interventions to eliminate any potential of confounding across arms due to counselor specific effects. The use of dedicated, specifically trained staff (as opposed to nurse or physician providers for example) is necessary because of the complexity of delivering all three of these treatments with high fidelity. While this diminishes generalizability of the results to primary care, meta-analyses suggest that the effects of MI are at least similar [13], if not improved, when delivered by general practitioners [12].

Training for MI consisted of refresher training in the practice and principles of MI through reading materials, video demonstrations, and a half-day training workshop; training in the MI protocol for the study (i.e., procedures and requirements for implementing MI in this study); and completion of role-play practice sessions with feedback from the MI arm supervisor in a group setting (i.e., with all counselors present). Counselors then practiced the MI protocol with pilot participants and received group supervision until they met criterion on rating scales designed for fidelity monitoring (described below) for 3 consecutive sessions.

Training for HE and BA was similar, including training in the HE and BA protocols for the study (i.e., procedures and content for implementing HE and BA in this study) and completion of role-play and pilot participant practice sessions accompanied by group supervision until 3 consecutive sessions met criterion.

#### Fidelity assurance procedures

All counseling sessions in the study are digitally recorded. Counselors alternate in receiving regular group supervision by separate expert supervisors (weekly for MI, every other week for HE, and monthly for BA). For each supervision session an audio-file is either randomly selected from those completed by the counselor since their last supervision session, or the counselor identifies a challenging session that they wish to receive feedback on. The supervisor provides verbal feedback as the group listens to the session and rates adherence to the respective protocols using rating scales adapted for this study. The rating scales assess procedural and content requirements for each arm. For example, the MI rating scales assess completion of basic procedures (e.g., remind the participant that the session is being audio recorded) and fidelity on 13 elements of MI (e.g., uses reflective listening, rolls with resistance vs. confronting, affirms and builds efficacy) and 1 global rating (how well did the counselor conduct the session). HE and BA rating scales similarly assess fidelity on basic procedures and key counseling elements (e.g., providing personalized advice, recommending quitting, linking participants’ symptoms to smoking). To externally verify that MI and HE sessions differ as expected, 10% of the MI and HE sessions (excluding those sessions that involve making quit plans which are expected to be quite similar) are randomly selected for coding on adherence to MI principles using the Motivational Interviewing Treatment Integrity code [26] by an expert independent coding group. Coders are blind to the study arm of the session and the study hypotheses. We anticipate that MI sessions will receive scores of 4 or higher on the 1–5 global rating and be significantly higher than HE sessions on ratings of evocation, collaboration, empathy, and autonomy support. With respect to frequency measures of counselor behavior we expect MI sessions to have a higher reflection to question ratio and significantly fewer instances of giving information.

### Randomization

Prior to starting enrollment a computer-generated randomization sequence was created by the project statistician that determines whether subjects will receive MI, HE, or BA in accordance with the 2:2:1 allocation ratio. The statistician used sequentially numbered opaque envelopes to conceal the group assignment sequence until randomization. Once eligibility is confirmed participants complete the informed consent process. The research assistant then opens the next numbered envelope in the sequence to reveal the participant’s group assignment and the participant begins the computerized baseline survey. In this manner all study personnel remain blind to the condition to which the participant is assigned until after participant’s eligibility is determined and informed consent is obtained.

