## Methods/Design

### Trial design

This is a multi-arm parallel group, randomized trial with imbalanced randomization (2:2:1 for MI, HE, and BA, respectively) being conducted in the United States. Blinding of counselors is not feasible in this study. Participants are informed that they will be randomly assigned to one of three counseling approaches that differ in style and/or number of sessions. Although participants can differentiate whether they are in the BA versus MI or HE because of the different number of sessions, they are not informed in any way regarding the names, the nature, or distinctions between HE and MI and therefore will be blind to which of these two treatments they receive.

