### Measures

Participants complete computer-administered assessments at baseline, week 12, and 6-month follow-up. Baseline variables include socio-demographic characteristics (gender, age, education, employment), smoking characteristics (cigarettes smoked per day, number of years smoking, number of prior quit attempts), level of nicotine dependence using the Severity of Dependence Scale [27], and single item measures of motivation and confidence to quit [28-30]. The primary outcome measure is the occurrence of any quit attempt defined as a serious quit attempt of at least 24 hours [31] by 6-month follow-up. The secondary outcome is biochemically verified 7-day point-prevalence abstinence at 6-month follow-up [32,33]. Biochemical verification is conducted by research staff using cotinine test strips for saliva [34]. Hypothesized mediators of MI’s effect on quit attempts are autonomous motivation and autonomy support which are assessed using the Treatment Self-Regulation Questionnaire [35] and the Health Care Climate questionnaire [36,37], respectively. For those who decide to make a quit attempt, weeks of pharmacotherapy use is assessed with a self-report checklist [29] and will be examined as a mediator of MI’s effect on cessation.

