#### Data analyses

All analyses will be conducted in an intent-to-treat manner. Our primary analyses will utilize a planned comparisons approach to compare the proportion of those making at least one quit attempt for HE and MI, and for BA and MI, using logistic regression. If preliminary analyses comparing groups on baseline variables suggest potential confounding effects by any covariate, these will be included in the logistic regression models. For the secondary hypotheses we will also use logistic regression to compare the effectiveness of HE and MI, and MI and BA, on 7-day point prevalence abstinence at follow-up. To evaluate autonomy support and autonomous regulation as mediators of the presumed effect of MI on quit attempts, and weeks of pharmacotherapy use as a mediator of the presumed effect of MI on cessation, we will follow the procedural steps outlined by Baron and Kenny [38] using logistic regression and the Sobel test [39,40].

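### The allocation envelope is opened before the baseline survey, so subjective baseline items that may become covariates in the primary models are collected after allocation, which matters mainly for MI versus BA

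*Protocol article*

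**What the plan says.** The Randomization section of the Protocol article sets out the order of the baseline visit. Eligibility is confirmed, consent is taken, and the envelope is opened by the research assistant, which discloses the "group assignment and the participant begins the computerized baseline survey". The safeguard it then claims is that study personnel stay blind "until after participant’s eligibility is determined and informed consent is obtained". The baseline assessment is not part of that safeguard.

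The Measures section lists the baseline variables: demographics, smoking characteristics, nicotine dependence by the Severity of Dependence Scale, and "single item measures of motivation and confidence to quit". Assessments are completed on a computer.

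Under Trial design, "Blinding of counselors is not feasible in this study", and "participants can differentiate whether they are in the BA versus MI or HE" from the number of sessions. As between the two intensive arms, "they are not informed in any way regarding the names, the nature, or distinctions between HE and MI".

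Under Data analyses, the primary comparisons (MI with HE, MI with BA) use logistic regression. Covariates are added if "preliminary analyses comparing groups on baseline variables" suggest confounding.

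**The concern.** A covariate measured before randomisation can differ between arms only by chance, so adjusting for it is safe. One measured after allocation is revealed can also differ because of the allocation. Motivation and confidence to quit are the items most open to this. They are subjective, they concern what the counselling is meant to change, and motivation plausibly predicts a quit attempt. A participant who learns that they will have one session of about 5 minutes, and not four of about 20, might answer them differently.

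The covariate rule compounds the problem. Because it looks for between-arm differences, it tends to pick up a variable that allocation has moved, and the baseline table cannot separate such a movement from chance imbalance. Adjusting for it would distort the MI versus BA estimate, one of the two planned primary comparisons.

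**Working it through.** This is mainly a check of the order of events. The plan gives no figure to reproduce.

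1. **Order of steps.** Phone pre-screen, then re-screen at the baseline visit (Recruitment section), consent, envelope, computerised survey (Randomization section). The survey follows the reveal; the eligibility screen precedes it.

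2. **Who knows the arm when the survey starts.** The research assistant does, by the text. For the participant, the document says only that BA can be told apart by its number of sessions, not when this is learned. Maximum payment also differs: BA 30 + 30 + 50 + 1 × 10 = $120, MI and HE 30 + 30 + 50 + 4 × 10 = $150 (Reimbursement section). Nothing says that the arm or session count is withheld until the survey is complete.

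3. **Which items could move.** Motivation, confidence and self-rated dependence. Age, gender, education and years of smoking could not plausibly do so.

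4. **Which comparison is exposed.** In MI versus HE, participants are told nothing that separates the arms, so the participant route is closed. In MI versus BA it is open if disclosure comes before the survey.

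5. **How a shift would reach the primary estimate.** If the item is adjusted for, the MI versus BA log odds ratio changes by approximately β × δ, where β is the log odds ratio of a quit attempt per SD of the item and δ is the allocation-induced difference in SDs. The document gives neither. As an illustration only, assume β = 0.8 and δ from 0 to 0.25:
   - δ = 0: 0.8 × 0 = 0, odds-ratio factor 1.00
   - δ = 0.10: 0.8 × 0.10 = 0.08, factor exp(0.08) = 1.08
   - δ = 0.25: 0.8 × 0.25 = 0.20, factor exp(0.20) = 1.22

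   The direction is unknown, since it depends on whether BA participants report more or less motivation on learning their arm.

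6. **How likely selection is.** The article gives no threshold, so assume a two-sided 5% test. With 102 MI and 51 BA participants, the standard error of a standardised difference is √(1/102 + 1/51) = 0.171. A shift of 0.10 SD gives z = 0.58 and would be flagged about 9% of the time. A shift of 0.25 SD gives z = 1.46, flagged about 31% of the time. With no shift the figure is 5%. On these assumptions the item would usually not be selected, and the primary estimate would then be unaffected by the order of steps.

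7. **What is available instead.** Eligibility requires 6 or less on a 0–10 motivation scale, and the re-screen takes place before consent and the envelope. A motivation score from before allocation therefore exists for every participant, but the Data analyses section does not say that it will be used.

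**The case against.** The case for leaving the plan alone is substantial. Only the research assistant is shown to know the arm, whereas it is the participant who answers, on a computer, which limits staff influence. The timing of disclosure is visit-level detail that a condensed article may leave to the full protocol. Bias needs a chain: disclosure before the survey, a real shift in answers, detection of that shift as imbalance, and entry of that item into the model. All of this stands, and it limits the point to a conditional risk in one comparison. It does not remove the point, because the article does state the order of envelope and survey, and that order leaves the first link open.

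A reader might go further in several ways that the document does not support:

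- *That the mediators are contaminated at baseline.* The autonomy questionnaires are not among the listed baseline variables and have no stated time point. Autonomy support concerns the counsellor, so it has little meaning before counselling starts.
- *That the survey values are not baseline values at all.* Nothing places counselling before the survey. The values are post-allocation but apparently pre-treatment.
- *That participants are lost between envelope and survey.* Both steps fall in one visit, and nothing indicates such loss.
- *That an odds-ratio distortion of 1.08 to 1.22 has been shown.* Those figures come wholly from assumed inputs, and zero is equally compatible with the text.

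**Conclusion.** The point holds in a limited form. As written, the subjective baseline items are collected after the research assistant is unmasked. If the arm or session count is disclosed at that moment, they are also collected after the participant can recognise BA. Because baseline differences choose the covariates, an allocation-induced shift could enter the primary models. The exposure is mainly in MI versus BA and low in MI versus HE.

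The size cannot be derived from the document. The conclusion rests on the stated sequence being followed literally and on no unstated step withholding the arm from participants. If the full protocol contains such a step, the participant route closes. The change is worth making because the risk is avoidable at almost no cost, not because bias has been demonstrated.

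**What to change.** 1. **Procedure.** For all remaining participants, complete and lock the computerised baseline survey before the envelope is opened, at the same visit. Enrolment is described as under way, so this can still help. It reorders two steps and adds no visit or measure.

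2. **Analysis.** Use the 0–10 motivation score from the pre-randomisation re-screen as the motivation covariate for every participant, early or late. Using it only for those already enrolled would make the covariate differ by enrolment period. This presupposes that the re-screen score was recorded as a number, which should be checked.

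3. **Covariate rule.** State that the other subjective survey items collected after allocation (confidence, self-rated dependence) are not eligible for selection as adjustment covariates. They can still be reported descriptively, marked as collected after allocation.

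The downside is small. Eligibility confines the re-screen score to 0–6, so it may be a somewhat weaker predictor than the survey item, with some loss of precision from adjustment.

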### Measures

Participants complete computer-administered assessments at baseline, week 12, and 6-month follow-up. Baseline variables include socio-demographic characteristics (gender, age, education, employment), smoking characteristics (cigarettes smoked per day, number of years smoking, number of prior quit attempts), level of nicotine dependence using the Severity of Dependence Scale [27], and single item measures of motivation and confidence to quit [28-30]. The primary outcome measure is the occurrence of any quit attempt defined as a serious quit attempt of at least 24 hours [31] by 6-month follow-up. The secondary outcome is biochemically verified 7-day point-prevalence abstinence at 6-month follow-up [32,33]. Biochemical verification is conducted by research staff using cotinine test strips for saliva [34]. Hypothesized mediators of MI’s effect on quit attempts are autonomous motivation and autonomy support which are assessed using the Treatment Self-Regulation Questionnaire [35] and the Health Care Climate questionnaire [36,37], respectively. For those who decide to make a quit attempt, weeks of pharmacotherapy use is assessed with a self-report checklist [29] and will be examined as a mediator of MI’s effect on cessation.

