### Recruitment, participants, and setting

The study is being conducted at a single university-based site in Kansas City, Missouri. The study protocol is in compliance with the Helsinki Declaration and was reviewed and approved by the Institutional Review Board of the University of Missouri – Kansas City (#0978). Smokers are recruited community-wide through word of mouth, newspaper ads, flyers, billboards, internet advertising, and physician referral using printed cards. Recruitment materials invite participation in a study “for smokers” or “smokers not quite ready to quit” and provide a study phone number to call for more information. Potential participants who enquire about the study are informed that the goal is to learn how best to talk to smokers about their health. They are informed that although their smoking will be discussed they will not be required to quit. Eligibility criteria are being 18 years or older, English speaking, reporting smoking a minimum of 1 cigarette per day, having a mailing address and telephone number, willingness to participate in all study components, not currently pregnant or planning to become pregnant in the next 6 months, not currently using a smoking cessation medication, not planning to move from the metropolitan area in the next 6 months, and not currently motivated or ready to quit smoking (defined as scoring 6 or less on a 0–10 point scale of motivation to quit smoking and having no intention to quit in the next 7 days). Potential participants are pre-screened by phone and those likely to be eligible are scheduled for a baseline visit at which time they are re-screened and enrolled if eligible. After the first 24 participants were enrolled, confirmation of self-reported smoking status using a carbon monoxide monitor (Bedfont Scientific piCO + Smokerlyzer®) was added to the re-screen. Eligibility is determined by a CO level of 7 ppm or higher [19,20].

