### Trial interventions

#### Motivational interviewing

MI consists of 4 sessions (baseline, week 6, week 12 and week 18) of approximately 20 minutes each conducted in-person (baseline and week 12) and over the phone (week 6 and week 18). The 4-session schedule is altered should participants set a quit date. All remaining sessions are scheduled on the day after the selected quit day and then every week after that. Although the optimal number of sessions of MI is not known [12,17] four sessions were chosen as a practical compromise between having too many sessions for participants who do not progress toward making a quit attempt and having enough sessions to both motivate and then assist smokers who do progress to making a quit attempt.

In MI counselors assist participants to explore and resolve ambivalence regarding quitting smoking, consistent with MI principles and strategies described by Miller & Rollnick [21]. MI emphasizes a collaborative, evocative, and autonomy supportive counseling approach, using specific communication skills (open-ended questions, affirmations, reflections, and summaries) to express empathy, develop discrepancy between client goals/values and current behavior, increase change talk, and “roll with” statements of resistance to change. MI sessions are characterized by a collaborative, interactive counseling style in which participants are engaged in the process of thinking and talking about their smoking behavior through the counselors’ use of strategic reflective listening and occasional open-ended questions and summaries. In MI, providing information on health-risks and the benefits of quitting is minimized and offered by counselors only when the participant asks for or appears clearly interested in the information.

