#### Provision of pharmacotherapy

All participants who set a quit date are offered pharmacotherapy to assist with their quit attempt to meet standard of care. Due to evidence of its potentially superior efficacy [23-25], counselors encourage the use of varenicline (Chantix®) when not contra-indicated. Participants who cannot or who do not wish to use varenicline are offered nicotine replacement therapy in the form of the patch or the lozenge. To avoid free medication serving as the primary motivator for smokers to quit, medication is not mentioned or offered to participants until after they have demonstrated a commitment to make a quit attempt by setting a quit date.

Participants who decide to use varenicline are provided with a 12-week supply (a starter pack and 2 continuation packs). Participants who choose chose the patch receive an 8 week supply if they smoke less than 10 cigarettes per day (14 mg for 6 weeks, 7 mg for last 2 weeks), a 10 week supply if they smoke 10 to 39 cigarettes per day (21 mg for 6 weeks, 14 mg for 2 weeks, 7 mg for 2 weeks), and a 10 week supply if they smoke 40 or more cigarettes per day (42 mg for 6 weeks, 28 mg for 2 weeks, and 14 mg for 2 weeks). Participants who choose the lozenge receive a 12-week supply (2 mg if they smoke their first cigarette 30 minutes after waking and 4 mg if they smoke within 30 minutes of waking). Participants are given instructions for the proper use of their medications at the time that medications are dispensed. Participants who decide to use medications during a phone counseling session are scheduled for a brief medication-dispensing visit. Participants with cautions for using varenicline (e.g., history of depression) are monitored closely for adverse events by means of weekly phone calls.

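### Six-month abstinence is verified only by saliva cotinine, so true abstainers still using trial-supplied nicotine patch or lozenge can fail verification

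*Protocol article*

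**What the plan says.** All references are to the protocol article.

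- **Outcome and test (Measures).** "The secondary outcome is biochemically verified 7-day point-prevalence abstinence at 6-month follow-up". The next sentence gives the method: "Biochemical verification is conducted by research staff using cotinine test strips for saliva". No second test is named, and nothing is said about participants using nicotine products at the visit.
- **Medication (Provision of pharmacotherapy).** "counselors encourage the use of varenicline (Chantix®) when not contra-indicated". Those who cannot or do not want to take it "are offered nicotine replacement therapy in the form of the patch or the lozenge". The patch supply lasts 8 weeks for the lightest smokers. Others get 10 weeks, for example "a 10 week supply if they smoke 10 to 39 cigarettes per day". For the other product: "Participants who choose the lozenge receive a 12-week supply".
- **When medication can start (Motivational interviewing, Health education, Brief advice).** In all three arms the offer applies to a quit date set at any point in planned participation. No earlier cut-off protects the 6-month test.
- **Sessions.** MI and HE have sessions at baseline and weeks 6, 12 and 18. BA has one session, at baseline.
- **Carbon monoxide (Recruitment, participants, and setting).** The re-screen includes "confirmation of self-reported smoking status using a carbon monoxide monitor", with 7 ppm or higher required for entry. No use of the monitor at follow-up is described.

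**The concern.** Cotinine is a breakdown product of nicotine from any source. This is general pharmacology and is not stated in the article. A positive strip therefore cannot separate someone who smokes from someone who has stopped and is using a patch or lozenge. The trial hands out those products on a timetable that can run past its own test date, so its verification method conflicts with a treatment it supplies.

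The cessation comparison is not powered. Its stated purpose (Abstract; Power and sample size; Discussion) is to supply effect-size estimates for a later trial, and for that use bias matters more than power.

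The mediation analysis is also exposed. Weeks of pharmacotherapy use is tested as a mediator of MI's effect on cessation, yet NRT use that continues to the visit can itself produce a failed test. That would pull the path from medication to cessation downward.

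**Working it through.** The article gives no expected cessation rate, power or sample size for this outcome, so there is no figure to reproduce. Two checks apply.

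**1. Can supplied NRT overlap the test?** Take 6 months as week 26 (assumption). The latest start that is finished by the test is 26 minus the supply in weeks, with the supplies from Provision of pharmacotherapy.

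| Product | Supply | Still in course at week 26 if started after |
|---|---|---|
| Lozenge | 12 weeks | 26 − 12 = week 14 |
| Patch, 10 or more cigarettes/day | 10 weeks | 26 − 10 = week 16 |
| Patch, under 10 cigarettes/day | 8 weeks | 26 − 8 = week 18 |

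Set against the sessions:
- NRT started at week 12 ends by 12 + 12 = week 24, so there is no overlap.
- NRT started at week 18 runs to week 30 (lozenge), week 28 (10-week patch) or week 26 (8-week patch).
- A quit date set at week 12 for more than two weeks ahead overlaps with lozenge use.
- In BA, a quit date near the baseline session ends supplied NRT by about week 12.

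The overlap is real but confined to late starters, plus anyone who uses NRT beyond the nominal course.

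**2. What does it do to the estimates?** Let f be the share of true abstainers on NRT at the visit, and assume all of them fail the strip. Then

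observed rate = true rate × (1 − f).

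The article gives neither true rates nor f. The values below are assumptions: true rates of 10% (MI) and 5% (comparator), with f from 0 to 30%. The true odds ratio is (0.10/0.90)/(0.05/0.95) = 2.11 and the true risk difference is 5 points.

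| f in MI | f in comparator | Observed rates | Risk difference | Odds ratio |
|---|---|---|---|---|
| 0 | 0 | 10% vs 5% | 5.0 points | 2.11 |
| 10% | 10% | 9% vs 4.5% | 4.5 | 2.10 |
| 20% | 20% | 8% vs 4% | 4.0 | 2.09 |
| 30% | 30% | 7% vs 3.5% | 3.5 | 2.08 |
| 20% | 10% | 8% vs 4.5% | 3.5 | 1.85 |
| 10% | 0 | 9% vs 5% | 4.0 | 1.88 |
| 20% | 0 | 8% vs 5% | 3.0 | 1.65 |
| 30% | 0 | 7% vs 5% | 2.0 | 1.43 |

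Worked example, 20% in both arms: (0.08/0.92)/(0.04/0.96) = 2.09. With 20% in MI only: (0.08/0.92)/(0.05/0.95) = 1.65. If the true rates were equal at 10% and 20% were lost in MI only, a spurious odds ratio of (0.08/0.92)/(0.10/0.90) = 0.78 would appear.

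Equal loss therefore lowers the rates and the risk difference but hardly moves the odds ratio, which is what the planned logistic regression estimates. Only unequal loss moves it materially.

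**The case against.** The case on the other side has several parts.

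- **Varenicline comes first.** It contains no nicotine and does not affect the strip, so only those who take patch or lozenge instead are exposed. This stands and limits the size.
- **The window is narrow.** NRT started at any of the first three sessions is finished before week 26. This also stands. Nothing in the article allows the affected group to be counted.
- **Arm differences are not shown.** A reader might infer that MI's effect against HE is attenuated, because medication use is a hypothesised mediator and so should differ by arm. The documents do not support that. The mediator is weeks of any pharmacotherapy, varenicline included, and says nothing about the share of abstainers on NRT at the visit. MI and HE share one schedule, format and medication offer. With equal shares the odds ratio stays near 2.1. A 30% versus 15% split would give (0.07/0.93)/(0.0425/0.9575) = 1.70, but that split is purely assumed.
- **No scoring rule is written.** The article does not say that an NRT user with a positive strip counts as a smoker, and the full protocol may hold an exception. This stands in part. However, the article makes verification part of the outcome and names one test without exception, so the point concerns a stated method and not missing detail.
- **CO has its own bias.** It reflects only recent smoking, so using it for NRT users alone is more lenient to them and could push the medication path upward. The 7 ppm figure is an entry threshold and is not offered as an abstinence criterion. Both remarks stand, and they shape the fix.

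**Conclusion.** The point holds, at moderate severity. The only stated verification can reject true abstainers who started trial-supplied NRT after about weeks 14 to 18, depending on product.

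- **Absolute cessation rates:** biased downward. The amount is unknown and is limited by the preference for varenicline.
- **MI versus HE:** the effect on the odds ratio is probably small (2.11 to 2.09 at an equal 20% loss), although the risk difference falls from 5 to 4 points.
- **MI versus BA:** could be biased against MI, because BA's only session is at baseline while MI prompts quit dates up to week 18. A 20% loss in MI alone gives 1.65. Zero loss in BA is the extreme case, since BA participants may also set a later quit date.
- **Mediation:** the path from weeks of pharmacotherapy to cessation may be biased downward.
- **Primary outcome:** self-reported quit attempts are unaffected.

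These figures rest on 6 months being week 26, on assumed true rates and NRT shares, and on every NRT user failing the strip. It would go too far to say that the effect sizes passed to the next trial will be wrong, or that any confirmatory conclusion is at risk. Cessation is a secondary outcome for which no power is claimed.

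**What to change.** Amend the outcome definition in Measures as follows.

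1. At the 6-month visit, ask every self-reported abstainer about use of any nicotine replacement in the past 7 days.
2. For those reporting use, verify by expired CO on the monitor already on site. Prespecify the abstinence cut-off, for example below the trial's own 7 ppm smoking threshold, and state that it is being adopted for this purpose.
3. Keep the cotinine strip for all other self-reported abstainers.
4. Take a CO reading from all self-reported abstainers, so that a sensitivity analysis can apply one common rule (for example CO for all) to both arm contrasts and to the mediation analysis.

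If the full protocol already has a rule for NRT users, stating it is enough.

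The cost is one question and a short breath test at a visit where saliva is already tested, with no new equipment. The drawback is that CO detects only recent smoking, so verification is somewhat more lenient in NRT users. The common-rule analysis shows how far that matters. The reading must be taken at the visit, because misclassified abstainers cannot be identified afterwards without it.
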